### Study Procedures

#### Baseline Evaluations and Data Collection

All eligible patients are comprehensively evaluated from three aspects by non-invasive methods: lumen stenosis, plaque characteristics, and hemodynamics. Magnetic resonance angiography (MRA) is preferred to assess lumen stenosis at supplemented target lesion, while other examinations, such as transcranial Doppler ultrasound, CT angiography, or digital subtraction angiography, could be used as an alternative. The measurement of stenosis degree will be defined by the WASID criteria (15). The location and length of the lesion are measured. As for the assessment of plaque characteristics, HR-MRI (an imaging technique for wall visualization) is planned to perform with 3 Tesla and 3D sequences to assess the arterial remodeling index, plaque burden, and signal intensity. Hemodynamics is quantitatively evaluated by the MRI technology of artery spin labeling (ASL). Hypoperfusion will be defined as regional cerebral blood flow <90% of normal flow referring contralateral territory (31). Arterial transit artifact on ASL is defined as a focus or curvilinear hyperintensity located bordering the region of perfusion defects, which is a highly sensitive indicator of cerebral ischemia (32).

In addition, CFD simulation is applied to analyze the three-dimensional properties of the blood flow, including translesional pressure drop, wall shear stress, and filtration rate of low-density lipoprotein for a comprehensive evaluation of hemodynamic features. The above multimodal imaging examinations are necessary to carried out at the time of recruitment. All imaging parameters are described in Online Supplementary Appendix I.

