### Patient Selection

Patients diagnosed with symptomatic ICAD (≥ 50% stenosis) in the anterior circulation in our center will be enrolled in this study from December 2021 to November 2024. Participants will be required to sign informed consent prior to data collection and documentation. All patients will receive the cerebral artery imaging examination. Patients with more than 50% of stenosis in the extracranial carotid on the ipsilateral side will be excluded through transcranial Doppler ultrasound. Detailed inclusion and exclusion criteria are described in Table 1.

**Table 1 T1:** Inclusion and exclusion criteria for patient selection.

**Inclusion criteria**	**Exclusion criteria**
1. Patients with symptomatic ICAS with culprit artery in the anterior circulation. 2. Patients aged from 18 to 80 years. 3. Stenosis of 50% to 99% (measured with WASID method) on TCD, CTA, or MRA initially, confirmed on DSA. 4. Informed consent is available from the patient or legal guardian.	1. Non-atherosclerotic lesion, for instance, moyamoya disease, vasculitis, vascular dissection, autoimmunity diseases, and developmental or genetic abnormalities. 2. More than 50% of stenosis in extracranial carotid on ipsilateral side. 3. Large cerebral infarction ( ≤ 1/2) identified by DWI and the baselin modified Rankin score of ≥3. 4. Antiplatelet drugs or statins are contraindicated. 5. MRI cannot be completed due to metal implants or claustrophobia.

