## Discussion

Intracranial atherosclerotic disease is the primary cause of stroke, especially in Asia, which caused high burdens of mortality and morbidity despite the latest treatment strategies, including medical management, endovascular treatment, and surgery (5). The effect of medical management seems ideal for a majority of patients with ICAD, while the current evaluation system cannot accurately predict those with a high risk of recurrent stroke under aggressive medical management (35). Although recurrent stroke is the multifocal cause in patients with symptomatic ICAD, studies have shown that the culprit lesion of ICAD was the major cause (36). Therefore, treatment for ICAD should be mainly focused on the culprit lesion. For the patients' refractory to medical management, other therapy strategies, such as endovascular treatment or surgery with direct intervention, has been adopted according to the current guideline recommendation (8, 13).

However, early diagnosis of high-risk patients' refractory to medical treatment and early triage to alternative therapy is limited by the current risk stratification system, which is merely based on the degree of luminal stenosis (37). The inclusion of the plaque characteristics and hemodynamics assessment with multimodal imaging method may provide a potential solution to make accurate risk stratification (22). To the best of our knowledge, the current study will be the first research to involve multimodal imaging evaluation from three aspects, including the degree of luminal stenosis, plaque characteristics, and hemodynamics, and plan to establish the prognosis prediction system for patients with ICAD who have medical treatment.

As an observational study, several potential limitations must be considered. The collected data may not be as robust as randomized control studies with blinding performance, while the randomized control studies may be needed to further confirm the results of the present study. Data collection and analysis will perform repeated verification and blinding assessment, respectively. Moreover, the study population will be focused on Chinese patients with ICAD; hence, caution must be applied when implementing the findings of this study in other ethnicities.

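### The degree of stenosis is confirmed on DSA for entry but taken from MRA, TCD, CTA or DSA at baseline, so the reading behind its score weight is not fixed

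*Protocol article*

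**What the plan says.** Protocol article, Patient Selection, Table 1, inclusion criterion 3: "Stenosis of 50% to 99% (measured with WASID method) on TCD, CTA, or MRA initially, confirmed on DSA". Read plainly, every enrolled patient has a DSA reading.

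Protocol article, Baseline Evaluations and Data Collection: "All eligible patients are comprehensively evaluated from three aspects by non-invasive methods", lumen stenosis being one of the three. The section continues: "Magnetic resonance angiography (MRA) is preferred to assess lumen stenosis at supplemented target lesion". It then names substitutes for MRA without ranking them: "such as transcranial Doppler ultrasound, CT angiography, or digital subtraction angiography, could be used as an alternative". One definition covers all of them: "The measurement of stenosis degree will be defined by the WASID criteria".

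Protocol article, Follow-Up Assessment, Table 3: CTA, MRA and DSA share one row, ticked at screening. There is no separate DSA row.

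Protocol article, Statistical Analysis: a multivariable logistic model is planned, and each variable's regression coefficient becomes its weight in the evaluation system.

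Protocol article, Discussion: early triage "is limited by the current risk stratification system, which is merely based on the degree of luminal stenosis". Stenosis is thus the index that the new score is meant to improve on.

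On the neck vessels, Patient Selection says: "Patients with more than 50% of stenosis in the extracranial carotid on the ipsilateral side will be excluded through transcranial Doppler ultrasound".

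**The concern.** DSA is compulsory in Table 1 and optional in the baseline section, where it also appears as an invasive option within an assessment called non-invasive. No order is given among the alternatives to MRA. A site following the text could score one patient on MRA, another on CTA and a third on TCD, and treat the values as the same variable.

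Naming WASID as the common definition does not cure this. WASID is a ratio of lumen diameters. MRA, CTA and DSA each show a lumen that can be measured, with their own errors. TCD records flow velocity, from which a diameter ratio cannot be read.

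Stenosis is not a minor covariate here. Modality-dependent error in it enters its coefficient, and the coefficient enters the score. A marker correlated with stenosis, such as translesional pressure drop, could take up part of the lost effect.

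The carotid exclusion is a different matter. Transcranial Doppler examines intracranial vessels, so it does not itself measure a stenosis in the neck. Under Endpoint Evaluation, a stroke is assigned to the responsible lesion by infarct location, in or out of the symptomatic artery's territory. A missed ipsilateral carotid lesion could cause an infarct in that same territory, which would be counted as a target-lesion event.

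**Working it through.** The plan gives no figure for agreement between modalities, so there is none to reproduce. The sample size of about 400 does not depend on this point.

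**Step 1. The sections side by side.**

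| Place | Role of DSA | Other modalities | WASID applied to TCD? |
|---|---|---|---|
| Table 1, criterion 3 | Confirms stenosis in every entrant | TCD, CTA or MRA first | Listed, but only before DSA confirmation |
| Baseline Evaluations | One alternative | MRA preferred; TCD or CTA also allowed | Yes, as a possible final reading |
| Table 3 | Shares a row with CTA and MRA | CTA, MRA | TCD not listed |

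The three places do not identify one stenosis reading per patient.

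**Step 2. How error in stenosis could act (illustration only).** Assumptions, none from the documents: standardised variables; reliability λ of measured stenosis; correlation ρ between true stenosis and a marker; random error; a marker measured without error and with no effect of its own.

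- Share of the true stenosis effect taken up by the null marker: ρ(1−λ)/(1−λρ²).
  - λ = 0.7, ρ = 0.5: 0.15/0.825 = 0.182.
  - λ = 0.5, ρ = 0.5: 0.25/0.875 = 0.286.
- Share left on measured stenosis: √λ(1−ρ²)/(1−λρ²). At λ = 0.7, ρ = 0.5: 0.837 × 0.75/0.825 = 0.76, a fall of about 24%.
- If the true odds ratio is 2 per SD of stenosis, the null marker shows exp(0.182 × ln 2) = 1.13, or exp(0.286 × ln 2) = 1.22 at λ = 0.5.

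**Step 3. What that would do to a test.** Evaluable patients: 400 × 0.9 = 360. Information on the marker coefficient is about 360 × 0.0898 × 0.9102 × (1−λρ²).

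- λ = 0.7: 29.4 × 0.825 = 24.3, standard error 0.203. The spurious log odds ratio 0.126 is 0.62 standard errors, so the chance of two-sided P < 0.05 is about 9.5% instead of 5%.
- λ = 0.5: 29.4 × 0.875 = 25.7, standard error 0.197. The shift is 0.198/0.197 = 1.0, and the chance is about 17%.

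**Step 4. Is the direction secure?** A logistic simulation of 400,000 records at the plan's 8.98% event rate, with stenosis reliability lowered from 1.0 to 0.6, gives:

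| Assumed setting (log-odds per SD) | Marker coefficient | AUC gain from marker |
|---|---|---|
| Both predictive (0.5 each), ρ = 0.3 | 0.50 to 0.55 | 0.039 to 0.060 |
| Both predictive, ρ = 0 | 0.50 to 0.50 | 0.053 to 0.064 |
| Stenosis 0.7, marker null, ρ = 0.5 | 0.00 to 0.16 | 0.000 to 0.005 |
| Both predictive, ρ = 0.3, marker reliability 0.6 | 0.37 to 0.41 | 0.024 to 0.038 |
| Both predictive, ρ = 0.5, marker reliability 0.6 | 0.33 to 0.44 | 0.015 to 0.035 |

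With no error in either variable, the gain is 0.039 at ρ = 0.3 and 0.028 at ρ = 0.5. Once the marker is also measured with error, its apparent gain stays below the error-free value at ρ = 0.3. At ρ = 0.5 it runs from below to above it. The net sign depends on quantities the article does not give.

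**The case against.** The strongest reply is that the plan describes two steps. Table 1 governs entry, and the baseline section opens with patients already eligible. DSA to admit a patient, then MRA to score the lesion, is coherent, and a score built on non-invasive imaging is a defensible aim. This explains the order, but not why TCD, CTA and DSA may stand in for MRA without a rule, nor how TCD can supply a WASID value.

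A second reply is that imaging parameters are sent to an online appendix, and an article may leave the choice of reading to a fuller document. Missing detail is indeed no finding. The point here is two stated rules that do not agree, and acquisition settings would not remove that.

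A reader might go further and infer that stenosis is mismeasured and the new markers will therefore look better than they are. The objection to that inference stands in full:

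- The article has no error data and does not say which reading enters the model.
- ASL, HR-MRI and CFD measures carry error too, which works the other way.
- If pressure drop is computed from the same scan as the stenosis reading, the errors are shared and the formula in step 2 does not apply.
- Statistical Analysis plans one multivariable model and no formal comparison with a stenosis-only model.

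A reader might also take the carotid wording as further evidence of a mismeasured predictor. It is not: it concerns who is enrolled and how events are attributed. It may also be loose wording for vascular ultrasound, since Table 1 names no modality for that exclusion and all patients receive cerebral artery imaging.

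**Conclusion.** The inconsistency is real and worth correcting. Table 1, the baseline section and Table 3 do not settle which stenosis reading is used, and TCD is admitted as a source for a measure it cannot provide. Mixed modalities may weaken the stenosis weight and shift part of it to correlated markers. The 18% shift, and the odds ratio of 1.13 for a null marker, are illustrations that rest entirely on an assumed reliability of 0.7, a correlation of 0.5 and an error-free marker. With zero correlation a null marker gains nothing. The documents do not support saying that the new markers will look better than they are.

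The carotid wording is a separate, smaller point about eligibility and attribution. The documents give no figure from which to size it.

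**What to change.** 1. Reconcile Table 1, the baseline section and Table 3, and name one WASID reading that enters the model for every patient.
   - If Table 1's DSA requirement stands, use that DSA reading. MRA, CTA and TCD then serve initial detection only.
   - If DSA is not in fact done in all patients, remove the confirmation requirement from Table 1 and fix one angiographic modality, for example MRA, for all.
2. In either case, remove TCD as a source of the WASID percentage.
3. Reconcile the transcranial Doppler wording for the extracranial carotid exclusion with the vessel imaging already obtained, and state which examination decides it.

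The cost is mainly wording. The first option needs no new procedure provided Table 1 is followed as written, but the stenosis term of the score would then no longer be non-invasive. The second option keeps the score non-invasive and gives up the angiographic confirmation that Table 1 promises.

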#### Treatment Management

All participants are treated with optimal medical therapy according to the guidelines for ICAD from the American Heart Association/American Stroke Association, which indicates medical management, including antithrombotic therapy and vascular risk factor management, as the first-line therapy (8, 13). Antithrombotic therapies include anticoagulant and antiplatelet agents, which are recommended for all patients with ICAD without contraindications. Anticoagulant agents are recommended for cardiogenic embolism. Antiplatelet agents are more commonly used in patients with ICAD compared with anticoagulant agents. A 3-month dual antiplatelet therapy (e.g., aspirin 100 mg per day and clopidogrel 75 mg per day) is recommended for patients with early-arriving minor stroke and high-risk TIA, while it is not suitable for long-term treatment. Then, single antiplatelet therapy, including aspirin or clopidogrel, is applied throughout their lifetime for the prevention of secondary stroke in patients with ICAD. In addition, all patients with ICAD are required to follow the vascular risk factor management, which comprises the management of low-density lipoprotein (LDL-C), blood pressure, blood glucose level [fasting glucose level and hemoglobin A1c (HbA1c)], and lifestyle changes, such as Mediterranean diet and physical activity (see Table 2). Mediterranean diet is a low-fat diet emphasizing monounsaturated fat, plant-based food, and fish consumption with salt limitation of fewer than 6 grams per day (8). All medical management will be directed and monitored through the internet or telephone by investigators.

**Table 2 T2:** The management of vascular risk factors and lifestyles.

**Risk factor and lifestyles**	**Target**
Blood pressure	<130/90 mmHg
LDL-c	<1.81 mmol/L (70 mg/dl)
Blood glucose	
Fasting	<5.9 mmol/L
HbA1c	<7%
Lifestyles	
Smoking cessation	Quitting smoking
Alcohol limitation	<2 times/week, <50 ml/time
Physical activity	Moderate-intensity aerobic activity more than 10 min 4 times a week or vigorous- intensity aerobic activity more than 20 min 2 times a week
Nutrition	Mediterranean-type diet with emphasis on a low-fat diet

#### Endpoint Evaluation

The primary endpoint of this study is be the ischemic stroke or death attributable to the lesion of the target vessel within 1 year after enrollment. The secondary endpoints are (1) any stroke or death; (2) all-cause mortality; (3) any stroke or death out of the territory of the responsible lesion, including hemorrhagic stroke, non-local ischemic stroke, and non-responsible vascular death; (4) functional outcome with the modified Rankin Scale (mRS).

Ischemic stroke is defined as the sudden onset of a new focal neurological deficit, such as hemiplegia, hemianopia, aphasia, dysphagia, sensory disorders, or confusion, lasting over 24 h, with new cerebral infarctions detected by MRI or CT. The classification of ischemic stroke for the responsible lesion is referred to as infarction location, as infarction in or out of the territory of the symptomatic intracranial artery. Hemorrhagic stroke is defined as the sudden onset of neurological deficits, with parenchymal, subarachnoid, or intraventricular hemorrhage detected by CT or MRI (33).

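### The primary endpoint is defined by cause, but strokes are assigned to the target lesion by infarct territory alone and a known cardioembolic source is not excluded, so some other-cause strokes can count as lesion failures

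*Protocol article*

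**What the plan says.** All references are to the Protocol article.

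- **Endpoint Evaluation** defines the primary endpoint by cause: "ischemic stroke or death attributable to the lesion of the target vessel within 1 year after enrollment".
- **The same section** gives one rule for assigning an ischemic stroke: "The classification of ischemic stroke for the responsible lesion is referred to as infarction location, as infarction in or out of the territory". The reference is the symptomatic artery's territory. It states no criterion on mechanism or competing cause. Secondary endpoint 1 is any stroke or death. Secondary endpoint 3 takes events outside the territory.
- **Patient Selection, Table 1**, which the text presents as the detailed criteria, requires "Patients with symptomatic ICAS with culprit artery in the anterior circulation". On competing causes it excludes "Non-atherosclerotic lesion, for instance, moyamoya disease, vasculitis, vascular dissection, autoimmunity diseases, and developmental or genetic abnormalities" and "More than 50% of stenosis in extracranial carotid on ipsilateral side". No cardiac source is listed.
- **Treatment Management** contains the sentence "Anticoagulant agents are recommended for cardiogenic embolism".
- **Discussion** states: "Although recurrent stroke is the multifocal cause in patients with symptomatic ICAD, studies have shown that the culprit lesion of ICAD was the major cause".
- **Follow-Up Assessment** says that all extracranial and intracranial arteries are evaluated at follow-up. Table 3, however, ticks vessel imaging only at screening and lists no cardiac work-up. Medical history is collected at screening.

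**The concern.** Cause and location are different criteria. The scheme has two classes, in or out of the territory, so an in-territory ischemic stroke from a cardiac embolus can only be classed with the responsible lesion. The carotid exclusion shows that the authors recognise that another source can feed the same territory. The same reasoning is not applied to the heart.

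The aim is to relate stenosis, plaque and hemodynamics of one lesion to failure of medical treatment at that lesion. The Statistical Analysis section turns regression coefficients directly into score weights. Strokes of another cause can distort those weights in two ways:

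- A predictor unrelated to the other cause loses strength.
- A variable that follows cardiac disease or age may enter the score as if it predicted failure of the lesion.

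**Working it through.** **The plan's own figure.** The only computed figure is a sample size of around 400. It cannot be reproduced uniquely, because power, sidedness and the share with compromised hemodynamics are not stated. For example, Schoenfeld's formula with 1:1 exposure and 80% power gives 33 events and N = 409 at one-sided 5%, but 41 events and N = 508 at two-sided 5%. This point does not dispute the figure. It uses only the inputs.

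**Inputs from the Sample Size section.** Hazard ratio 2.4 for compromised hemodynamics, 1-year ischemic stroke recurrence 8.98%, loss 10%, N = 400. Expected events: 400 × 0.9 × 0.0898 = 32.3. The 8.98% is not described as lesion-attributable, so a stricter endpoint would yield fewer.

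**Assumptions, not in the article.**
- Exposed share a = 0.5, two-sided alpha 5%.
- f = share of in-territory strokes with another cause.
- h = hazard ratio of the predictor for those other-cause strokes.

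**Formula.** Set the unexposed lesion hazard to 1 and the exposed to 2.4. The mean is L = (1 − a) + 2.4a = 1.7. The other-cause hazard in the unexposed is c = [f/(1 − f)] × L / (1 − a + h·a). The observed HR is (2.4 + c·h)/(1 + c).

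**Unrelated other-cause strokes (h = 1).**
- f = 5%: c = 1.7 × 0.05/0.95 = 0.089; HR = 2.489/1.089 = 2.29
- f = 10%: c = 0.189; HR = 2.589/1.189 = 2.18
- f = 20%: c = 0.425; HR = 2.825/1.425 = 1.98
- f = 30%: c = 0.729; HR = 3.129/1.729 = 1.81

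Of 32.3 events, these shares are about 1.6, 3.2, 6.5 and 9.7 strokes. With a = 0.3 the results are close: 2.21 at 10% and 2.03 at 20%.

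**Predictor also related to the other cause (f = 20%, a = 0.5).**
- h = 1.5: c = 0.25 × 1.7/1.25 = 0.34; HR = (2.4 + 0.51)/1.34 = 2.17
- h = 2.4: c = 0.25; HR = (2.4 + 0.60)/1.25 = 2.40, so no dilution

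**Power.** Schoenfeld: Φ(√(E·a(1 − a)) × ln HR − 1.96). With no contamination, √(32.3 × 0.25) × 0.875 − 1.96 = 0.53, which is 70%. The last two columns assume that every other-cause stroke is recognised and left out.

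| f (h = 1) | HR, territory only | Power | Events after removal | Power at HR 2.4 |
|---|---|---|---|---|
| 5% | 2.29 | 65% | 30.7 | 68% |
| 10% | 2.18 | 60% | 29.1 | 66% |
| 20% | 1.98 | 49% | 25.9 | 60% |
| 30% | 1.81 | 39% | 22.6 | 55% |

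If h = 2.4, removal only loses events: at f = 20% power falls from 70% to 60%. The planned model is logistic. The hazard ratio is used here because the sample size is stated in that form.

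**The case against.** **Territory is a defensible rule.** It is objective and reproducible. A rule based on mechanism adds judgement, and an assessor who knows the stenosis or plaque findings could build the predictors into the outcome. With no cardiac work-up in Table 3, such a rule would also be applied unevenly. This stands, and it is why the territory rule should not be replaced outright.

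**Not every imaging predictor is necessarily diluted.** A reader might infer that all are. That requires other-cause strokes to be independent of each predictor. The Introduction says that hypoperfusion impairs washout of debris, so emboli from elsewhere might also cause infarction more often in a hypoperfused territory. The h = 1.5 and h = 2.4 results above show the consequence.

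**The share may be small.** The Discussion calls the culprit lesion the major cause of recurrence, and the culprit-artery criterion and the carotid exclusion remove part of the competition. Nothing in the article favours 10% to 30% over 0% to 5%. This stands for the size of the effect. The culprit-artery criterion, however, concerns the qualifying event and does not settle the cause of a later stroke.

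**Enrolment of cardioembolic patients is not proved.** A reader might infer from the anticoagulant sentence that such patients are expected in the cohort. It sits in a summary of guideline advice and does not say so. The point rests on the absence of a cardiac criterion in Table 1 together with the stated stroke rule.

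**The article is condensed.** Detailed adjudication rules may lie in a full protocol. That is fair for what is left unsaid, but the location rule and the Table 1 list are stated here and can be judged as they stand.

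**Conclusion.** The concern holds in a limited form. An endpoint defined by cause is put into effect by a rule on location, and one competing source is screened out at entry while another is not. As written, an in-territory cardioembolic stroke would count as failure of the lesion.

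The direction is toward 1 for predictors unrelated to the competing cause. For variables that follow cardiac disease or age, a spurious place in the score is possible. The size cannot be derived from the article. Under a true HR of 2.4, a 50/50 split and h = 1, the observed HR runs from about 2.29 at a 5% share, a small loss, to 1.81 at 30%. If h rises to 2.4 the loss disappears. The article supports neither dilution of all predictors nor any particular share.

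**What to change.** 1. Add to Table 1 an exclusion for a known cardioembolic source at entry, taken from the medical history already collected.
2. Keep infarct territory as the rule for the primary endpoint.
3. Prespecify an added analysis that does not count in-territory strokes with another definite cause documented in the available event records. The classification is made blind to the baseline imaging predictors. These strokes remain in secondary endpoint 1.

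**Cost.** One eligibility line and one analysis sentence. A few patients become ineligible. The added analysis has slightly fewer events, for example 30.7 instead of 32.3 at a 5% share. Competing causes will be found only as far as routine records allow, because Table 3 schedules no cardiac work-up and no vessel imaging after screening. The added analysis therefore reduces misclassification but does not remove it.
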